## Statistical methods

### Statistical methods for primary and secondary outcomes {20a}

#### General analytic procedures

The superiority of the Mind programme over the control group(s) will be tested through the analysis of changes in the primary (cancer-specific QoL) and secondary outcomes (anxiety and depressive symptoms, psychological flexibility, self-compassion, health-related QoL, resources consumption), controlling for sociodemographic and clinical variables and potential moderation effects of variables such as the awareness of psychological processes, the frequency of at-home practice, the number of major life events occurring during the previous year and efficacy expectancy. The Mind programme will be compared against the support group in study 1 and against both the support and treatment as usual (waiting list) groups in study 2. Study 1 also includes immunological and epigenetic markers as secondary outcomes. The analytical approaches for both studies are otherwise comparable.

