The within-trial economic analyses will be carried out in line with standard health economic methods, following the Consolidated Health Economic Evaluation Reporting Standards (CHEERS) checklist [56]. An economic evaluation of each trial will be conducted. Each economic evaluation will include a cost-utility analysis using the outcome quality adjusted life years (QALYs). EQ5D-5L utility scores will be used to estimate QALYs over each trial period using the area under the curve method [57]. Costs will be estimated from two different perspectives, a Portuguese public health care system perspective and a societal perspective. Costs within the public health care system perspective include the cost to run the interventions, including, for instance, therapist costs, as well as other health care costs (other health care utilisation and medication use). In the analysis from a societal perspective, costs beyond the healthcare sector will additionally be included, for instance, social support, and indirect costs (e.g. productivity loss associated with work absenteeism) captured by the UKCC. Costs will be estimated using publicly available unit costs for healthcare services, market process for medications and lost wages for absence from work. Costs per participant will be calculated by multiplying the frequency of each resource by its unit cost. Unit costs will be sourced from publicly available sources.

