Costs and QALYs between the Mind programme and the control groups will be compared. Differences in QALYs and costs between the groups will be analysed using generalised linear models to allow for other distributions and functional forms to fit the cost and QALY data [58]. Incremental cost-effectiveness ratios (ICERs) will be estimated, as the ratio between the difference in costs and the difference in QALYs between the Mind programme and the control groups, for each costing perspective. The ICERs will be expressed as additional costs per additional QALY gained. Non-parametric bootstrapping will be carried out to deal with uncertainty around the incremental cost and QALY estimates, which will be represented on cost-effectiveness planes. A cost-effectiveness plane is a scatterplot of the bootstrapped estimates across four quadrants, where each quadrant has a decision implication. Net monetary benefits at different thresholds of willingness to pay will be calculated to determine the proportion of times the Mind programme yields more net benefit than the controls. These proportions will be plotted to generate cost-effectiveness acceptability curves (CEAC), which show the probability of the intervention being cost-effective at different values a decision-maker is willing to pay for a unit of improvement, in this case, a QALY gained [59, 60]. One-way sensitivity analyses will be carried out to test for the impact of changes in assumptions on the robustness of the results.

Aim 3: Determine the contribution of mediators and moderators in treatment effect.

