#### Covariates (controlling variables)

Where variables are expected to correlate with but not differentially predict outcomes, we will control for the influence of expected covariate variables by including them at the baseline model. The planned covariates consist of sociodemographic and clinical variables, such as age, education level, marital status, type of BC, BC stage, previous chemotherapy treatment, use of psychopharmacological medication, time since diagnosis, recurrence and number of major life events occurring during the previous year.

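### Baseline EQ-5D-5L utility is not named as a covariate in the QALY comparison; specifying it would sharpen incremental QALYs and remove the expected effect of chance baseline imbalance

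*Protocol article*

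**What the plan says.** All references are to the protocol article.

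- **Analyses by aims, Aim 2.** On constructing the outcome: "EQ5D-5L utility scores will be used to estimate QALYs over each trial period using the area under the curve method". On comparing it: "Differences in QALYs and costs between the groups will be analysed using generalised linear models to allow for other distributions and functional forms". The only reason given for the model is distributional fit. The ICER is defined "as the ratio between the difference in costs and the difference in QALYs between the Mind programme and the control groups", followed by non-parametric bootstrapping, cost-effectiveness planes and acceptability curves. On robustness: "One-way sensitivity analyses will be carried out to test for the impact of changes in assumptions on the robustness of the results". Baseline adjustment is not mentioned there.
- **General analytic procedures.** Outcomes, including health-related QoL and resource consumption, are analysed "controlling for sociodemographic and clinical variables", together with possible moderators.
- **Covariates (controlling variables).** "The planned covariates consist of sociodemographic and clinical variables, such as age, education level, marital status, type of BC, BC stage, previous chemotherapy treatment". The list continues with further items of the same kind and with the number of major life events.
- **Outcomes {12} and Planned moderation analysis variables.** These add process awareness, home practice and efficacy expectancy as possible covariates or moderators. No baseline outcome score is among them.
- **Sequence generation {16a}.** Randomisation is stratified by chemotherapy only, so utility is not balanced by design.

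**The concern.** An area-under-the-curve QALY contains the baseline utility as its first point, and the later utilities correlate with it. If one arm happens to start with better utility, it will tend to show more QALYs whatever the treatment does. The efficacy analysis under Aim 1 keeps baseline as one of three repeated measures and looks at change over time. Aim 2 collapses the visits into a single total, so that protection is lost unless baseline utility enters the QALY model.

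Incremental QALYs are the denominator of the ICER and drive net benefit, and superiority in cost-effectiveness is one of the stated hypotheses. The arms are small, about 75 per arm in study 1 and about 61 v 31 for Mind against usual care in study 2, so chance differences in baseline utility are not negligible. If the covariate is left open, the choice between an adjusted and an unadjusted ICER may also be made after the data are seen.

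**Working it through.** **The plan's own figures.** The article gives no figure for QALYs, utility SD or baseline imbalance. The nearest, study 1's detectable SMD of 0.51, reproduces at 60 per arm (20% attrition, within the stated 10-30%): (1.960 + 0.842) × √(2/60) = 0.511. It does not depend on the QALY model.

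**Inputs from the article (Sample size {14} and the intervention description)**
- Three assessments; 8 weekly sessions, so post-treatment falls at about 2 months.
- Correlation 0.5, compound symmetry. This is stated for cancer-specific QoL, not for EQ-5D.
- Study 1: 75 v 75. Study 2: N = 153 at 2:2:1, so 153 × 2/5 ≈ 61 and 153/5 ≈ 31.

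**Assumptions**
- Utility SD 0.20, equal at all visits.
- EQ-5D-5L measured at all three visits (Table 3 is not reproduced).
- Final visit at 8 months, that is, 6 months after post-treatment. A 26-week endpoint is also shown, because the anchor is unclear.
- Correlation ρ from 0.5 to 0.7.

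**Step 1: trapezoid weights (years), visits at 0, 2 and 8 months.** w0 = 1/12, w1 = 4/12, w2 = 3/12.

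**Step 2: carry-over per unit of baseline imbalance = w0 + ρ(w1 + w2).**
- ρ = 0.5: 1/12 + 0.5 × 7/12 = 0.375
- ρ = 0.7: 1/12 + 0.7 × 7/12 = 0.492
- With a 26-week endpoint (weights 0.077, 0.250, 0.173): 0.288 and 0.373

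The overall range is about 0.3 to 0.5. The direct weight of baseline utility itself is only about 0.08 years; the rest comes through correlation.

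**Step 3: precision.** QALY variance in units of SD² is Σw² + 2ρΣwᵢwⱼ = (26 + 38ρ)/144.
- ρ = 0.5: 45/144 = 0.3125; R² = 0.375²/0.3125 = 0.45; SE ratio √0.55 = 0.74, a cut of 26%.
- ρ = 0.7: 52.6/144 = 0.365; R² = 0.492²/0.365 = 0.66; SE ratio 0.58, a cut of 42%.

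With weekly timing at ρ = 0.5, R² is 0.443 (week 34) or 0.478 (week 26), so the cut is 25% or 28%. These percentages do not depend on the assumed SD.

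**Step 4: size of a one-standard-error imbalance.**

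| Comparison | SE of baseline difference | QALY shift, ρ = 0.5 | QALY shift, ρ = 0.7 |
|---|---|---|---|
| Study 1, 75 v 75 | 0.20 × √(2/75) = 0.033 | 0.012 | 0.016 |
| Study 2, Mind v usual care, 61 v 31 | 0.20 × √(1/61 + 1/31) = 0.044 | 0.017 | 0.022 |

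The shifts scale in proportion to the assumed SD. Relative to the standard error of the unadjusted estimate, a one-SE imbalance moves the result by √R² = √0.45 = 0.67 at ρ = 0.5, whatever the SD.

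**Step 5: comparison effect.** A true 0.05 utility gain at both later visits is worth 0.05 × 7/12 = 0.029 QALY. At ρ = 0.5 the shifts are 0.01225/0.02917 = 42% of that (study 1) and 0.01654/0.02917 = 57% (study 2).

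**The case against.** The strongest reply is that this is silence, not error. No sentence says the QALY model is unadjusted. The covariate list gives examples rather than an exhaustive set, and the economic section promises that "The within-trial economic analyses will be carried out in line with standard health economic methods" and follows CHEERS. A condensed article may leave the covariates of a secondary model to a fuller plan. This stands to the extent that a reader might infer that the sponsor has decided against baseline adjustment, and the documents do not support that. What remains is that the article does state a covariate plan, describes its class as sociodemographic and clinical, adds several process and expectancy variables, and never reaches the variable most closely tied to the QALY total.

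Three other inferences are tempting and should be resisted:

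- **That the unadjusted estimate is biased.** Under randomisation it is unbiased on average, and the bootstrap reflects its extra variance. The harm is lost precision, plus a shift conditional on the imbalance that actually occurs.
- **That imbalance passes through in full.** The carry-over is about 0.3 to 0.5 QALY per unit.
- **That ordinary imbalance equals a plausible treatment effect.** In study 1 at ρ = 0.5, matching 0.029 QALY would need 0.02917/0.01225 ≈ 2.4 standard errors of imbalance.

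**Conclusion.** The concern holds as a gap in specification with a worthwhile remedy. The article does not name baseline EQ-5D-5L utility as a covariate for the QALY comparison, and no covariate named elsewhere is a baseline outcome score. If the model is run that way, the result is valid on average but less precise than it need be, and it is exposed to chance imbalance that the ICER, plane and acceptability curve then inherit.

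The firmest figure is the precision gain at ρ = 0.5, about 25-28% off the standard error. It needs no utility SD, but it borrows a correlation planned for a different QoL measure. The absolute shifts of about 0.012 and 0.017 QALY rest on the assumed SD of 0.20 and the assumed visit months. They are material beside 0.029 QALY but smaller than it. Attrition would enlarge them, because the baseline standard error grows as the analysed arms shrink.

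**What to change.** Add to the Aim 2 text, after the sentence on generalised linear models, wording to this effect:

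> QALY differences will be estimated by regression adjusted for baseline EQ-5D-5L utility in addition to the planned covariates. The same adjusted model will be refitted in every bootstrap sample used for the ICER, the cost-effectiveness plane and the CEAC.

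Previous chemotherapy, the stratification factor, is already among the planned covariates and needs no separate addition. If a fuller analysis plan already contains this adjustment, a short statement of it in the protocol is enough.

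The cost is one model term. The area-under-the-curve calculation already requires the baseline utility, so there are no new data, visits or participants. It should be fixed before outcome data are examined by arm.

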### Objectives {7}

Both randomised controlled trials (RCT) presented in this manuscript aim to determine the efficacy (aim 1) and cost-effectiveness (aim 2) of an optimised version of the Mind programme, an integrative ACT and compassion-based intervention tailored for women with BC, compared to an active (i.e. support group) and/or inactive (i.e. treatment as usual group) control condition. These trials also aim to determine the contribution of mediators (e.g. psychological flexibility) and moderators (e.g. age) factors in treatment effect (aim 3). Efficacy indicators comprise cancer-related quality of life (primary outcome), anxiety and depressive symptoms, psychological flexibility, self-compassion, health-related quality of life, and intervention’s acceptability and feasibility (secondary outcomes). Cost-effectiveness indicators cover participants’ costs and resource utilisation outside the hospital setting (secondary outcome). Immunological and epigenetic markers (secondary outcomes) will also be considered (study 1).

The following hypotheses will be tested: (1) women with BC receiving the Mind programme will show increased levels of psychosocial and biological outcomes than those in the control group(s); (2) the Mind group will demonstrate superiority in a cost-effectiveness analysis compared to the control group(s); (3) changes in specific secondary outcomes (e.g. psychological flexibility) will mediate treatment effects on women cancer-related QoL with some characteristics (e.g. older, educated).

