### Intervention description {11a}

#### Mind programme for women with BC (optimised version)

The Mind programme is a manualised psychological intervention tailored to women with BC and intended to be delivered by two licenced psychologists, in a face-to-face or online group format. This intervention comprises 8 weekly group sessions, lasting 90–120 min each. Its content was optimised by the research team based on (a) the intervention’s pilot study results [30]; (b) the research team’s experience in psycho-oncology and/or in delivering similar interventions to patients with chronic medical conditions; (c) previous clinical experience in delivering the Mind programme in its pilot study; and (d) previous clinical experience in delivering the LIFEwithIBD programme, an adaptation of the Mind programme for people with inflammatory bowel disease [31, 32] As part of optimising the intervention (Table 1), modules on shame and self-criticism were improved, and the forgiveness module of the original Mind programme was replaced with a module on gratitude. Some compassion strategies (e.g. Compassionate Image exercise) were replaced by Mindful Self-Compassion practices, and the module on the observing self, as conceptualised by ACT, was removed [33]. Therefore, the optimised Mind programme (Table 1) comprises the following core themes: (a) acceptance of internal experiences, willingness, values and committed action [34]; (b) mindfulness practice [35]; (c) compassion-based practices [e.g. Mindful Self-Compassion [33], Compassion-Focused Therapy [23] and Loving Kindness meditation [36]; and (d) gratitude (towards one’s body) [36]. Educational aspects of physical and mental fatigue were also included. Each session will follow a similar format: (1) meditation practice; (2) discussion about between-session assignments (homework); (3) presentation of the session’s topics and in-session experiential exercises and practices; and (4) mindfulness or compassion meditation practices. Participants will have access to a participants’ manual (including handouts and audio files), which will guide them over the sessions and exercises. The between-session activities (e.g. mindfulness exercises and compassion practices, available through audio files made available through the sessions) are in line with the topics covered in each session and are prescribed to participants for daily practice until the next session. Participants with two missed sessions will be considered intervention non-completers, but they will be allowed to maintain their participation (and included in intention-to-treat analyses). To ensure treatment integrity, the following will be assured: (a) the Mind programme will be delivered in a co-therapy system, by two therapists with (at least) a Portuguese psychologist licence, a MSc degree in Clinical Psychology, and experience and training in ACT, mindfulness and compassion-based interventions; (b) all therapists will follow the intervention manual; (c) by the end of each session, the co-therapist will complete a checklist of the contents discussed in each session to safeguard treatment fidelity.

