#### Support group intervention

This intervention (comparator) comprises 8 weekly 90 to 120-min sessions intended to be delivered by two licenced psychologists, in a face-to-face or online group format. Table 2 presents the BC-related content of the intervention, which will be discussed among participants in each session. The facilitators of this intervention will engage in a purely moderating role (e.g. facilitators should guarantee that all the participants have the chance to participate, and no one will use that time extensively; facilitators should also intervene if a participant states inaccurate information). As it is the case with the Mind programme group, participants with two missed sessions will be considered intervention non-completers, but they will be allowed to maintain their participation (and included in intention-to-treat analyses).

**Table 2 Tab2:** Session content for the support group intervention

Session 1	Participant self-introduction, group rules and discussion of expectations related to the intervention
Session 2	Emotional impact of BC diagnosis
Session 3	BC treatment side effects
Session 4	BC impact on family and caregivers
Session 5	Work-related and physical impact of BC (e.g. fatigue)
Session 6	Body image and sexuality after BC
Session 7	Self-care strategies
Session 8	Conclusion and final remarks

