#### Treatment as usual (waiting list)

The inactive control group (study 2) will receive the usual treatment for cancer patients in Portugal. In this country, the public healthcare system does not offer psychological counselling or psychotherapy as part of the regular care of women with BC. To gain access to this service, a referral from a physician is needed and not always granted due to lack of resources. At the end of this project, the intervention that proves to be most efficacious will be offered to the participants allocated to this condition.

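### The economic contrasts as stated cannot show the public payer whether Mind is worth adding to current care in study 1, and do not compare the three options jointly in study 2

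*Protocol article*

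**What the plan says.** The Aim 2 text under Analyses by aims in the protocol article fixes four things.

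- **Unit.** "An economic evaluation of each trial will be conducted", so study 1 has its own result.
- **Perspective.** Costs are taken from "a Portuguese public health care system perspective and a societal perspective".
- **Delivery cost.** "Costs within the public health care system perspective include the cost to run the interventions, including, for instance, therapist costs".
- **Contrast.** The ICER is "the ratio between the difference in costs and the difference in QALYs between the Mind programme and the control groups, for each costing perspective". Net monetary benefit and the acceptability curve likewise set Mind against the controls.

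General analytic procedures gives the comparators: the support group in study 1, and both the support group and TAU in study 2.

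The two active arms have the same timetable and staffing. Mind is "intended to be delivered by two licenced psychologists, in a face-to-face or online group format. This intervention comprises 8 weekly group sessions, lasting 90–120 min" per session. For the support group: "This intervention (comparator) comprises 8 weekly 90 to 120-min sessions intended to be delivered by two licenced psychologists", also in a group format. Under Explanation for the choice of comparators, the support group is there to control for belonging to a group, sharing experiences and contact with therapists.

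On current care, the section on treatment as usual says that "the public healthcare system does not offer psychological counselling or psychotherapy as part of the regular care of women with BC". Access needs a physician's referral, which is not always granted.

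Hypothesis 2 (Objectives) expects Mind to be superior to the control group(s) in a cost-effectiveness analysis.

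**The concern.** A public payer deciding whether to fund Mind needs to know what Mind adds, in cost and in QALYs, to the care it funds now. In study 1 the analysis counts therapist cost and then subtracts an equal number of therapist hours, because the only comparator uses them too. The study 1 ICER and acceptability curve therefore do not respond to the largest planned input of the programme. If they are read as a public health care system result, they answer a different question from the payer's.

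Study 2 has the comparator that the payer needs. With three mutually exclusive options, however, contrasts of Mind with each control are not a complete comparison. Support against TAU is missing, so the text has no step that shows whether support is itself a reasonable use of money or should leave the ranking. Two pairwise curves also do not add up to the probability that Mind is the best of the three.

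At stake is what each trial may claim under Aim 2. The primary efficacy analysis is not affected.

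**Working it through.** The article states no unit cost, QALY difference, willingness-to-pay threshold or ICER, so there is no figure of its own to reproduce. The check is algebraic, followed by two illustrations on assumed values.

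**1. Scheduled therapist time** (intervention descriptions of both arms)

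8 sessions × 2 psychologists × 1.5 h = 24 h; 8 × 2 × 2 h = 32 h. That is 24 to 32 psychologist-hours per group course in Mind and the same in support.

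**2. What remains in each contrast**

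Per woman, let C be the delivery cost common to both active arms, m the Mind-only extras (manual, audio files, homework reminders, any difference in therapist rate), and H_M, H_S, H_T the other health care costs.

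- Mind v support: (C + m + H_M) − (C + H_S) = m + (H_M − H_S). C cancels.
- Mind v TAU: C + m + (H_M − H_T). C stays.
- Support v TAU: C + (H_S − H_T). This is not among the stated contrasts.

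The cancellation needs no assumed values.

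**3. Illustration of the cancellation**

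Assumed: groups of 6 to 12 women, EUR 15 to 40 per therapist-hour, m = 0, equal other costs, QALY gain 0.005 v support and 0.010 v TAU, threshold EUR 20,000 per QALY.

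C runs from 24 × 15 / 12 = EUR 30 to 32 × 40 / 6 = EUR 213 per woman.

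| C (EUR) | Mind v support: ICER | Net benefit | Mind v TAU: ICER | Net benefit |
|---|---|---|---|---|
| 30 | 0 / 0.005 = 0 | 100 − 0 = +100 | 30 / 0.010 = 3,000 | 200 − 30 = +170 |
| 100 | 0 | +100 | 10,000 | +100 |
| 213 | 0 | +100 | 21,300 | −13 |

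The support contrast is flat in C. The TAU contrast is not.

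**4. Illustration of three options**

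Assumed, per woman v TAU: support +EUR 300 and +0.005 QALY; Mind +EUR 330 and +0.012 QALY. These values were chosen to show the mechanism.

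- Mind v support: 30 / 0.007 = EUR 4,286 per QALY.
- Mind v TAU: 330 / 0.012 = EUR 27,500 per QALY.
- Support v TAU: 300 / 0.005 = EUR 60,000 per QALY.

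The step from TAU to support costs more per QALY than the step from support to Mind, so support is extendedly dominated. The neighbours on the frontier are then TAU and Mind, with an ICER of 27,500. At EUR 20,000 per QALY the net benefits are TAU 0, support 100 − 300 = −200, Mind 240 − 330 = −90. Mind beats support by 110 and loses to TAU by 90.

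**5. Why two curves are not one**

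Let p1 be the probability that Mind has more net benefit than support, and p2 the same against TAU. The probability that Mind beats both lies between max(0, p1 + p2 − 1) and min(p1, p2). The two curves alone do not locate it within that range.

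**6. Precision with TAU**

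Under 2:2:1 allocation and equal variances, the variance of Mind v TAU relative to Mind v support is (1/2 + 1/1) / (1/2 + 1/2) = 1.5. The standard error is √1.5 = 1.22 times as large.

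**The case against.** The strongest reply has five parts.

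- **Study 2 includes TAU.** This stands. Mind against TAU is planned with full delivery cost. A reader might infer that Mind can look cost-effective whatever it costs the health system. The documents do not support that: it describes only the support contrast, and there Mind must still show a QALY gain or a saving over an active control.
- **Incremental cost is not zero.** This stands too. Mind has its own materials and reminders, and its therapists must have a master's degree and specific training that the support group description does not ask for. Other care may differ as well. Only scheduled hours are shown to be equal, not total cost.
- **Net benefit already answers the question.** If Mind has more net benefit than both controls, it is the best option, as a full ranking would also find. In the second illustration the plan would report that Mind loses to TAU, so the inference that the conclusion reverses is not supported unless a planned contrast is ignored. If the net-benefit sentence means beating both controls in the same bootstrap sample, Mind's probability is the right one. The article does not say so, and the ICERs still omit support against TAU.
- **An article condenses.** It commits to standard economic methods and a reporting checklist, and a full analysis plan may hold the ranking steps. That is fair for layout and algorithm. But the article itself fixes the perspective, one evaluation per trial and the contrasts, and the point is about those.
- **Study 1 names its comparator openly, and hypothesis 2 refers to the control group(s).** Correct: the article makes no false claim about study 1. Usual care is also not strictly free of psychological help, given referral. Even so, a public-payer label on a result that omits the cost of adding the service invites misreading.

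**Conclusion.** The point holds in a limited form. In study 1, and in the Mind-against-support contrast of study 2, the shared delivery cost (24 to 32 psychologist-hours per group course) cancels. That contrast is valid as stated, but it is not evidence on whether adding Mind to current Portuguese care is worth its cost to the public payer. In study 2 the right comparator is present, but the stated pairwise contrasts leave out support against TAU and, if run as separate curves, do not give the probability that Mind is the best of the three.

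The cancellation rests on equal scheduled sessions and staffing, and is exact for the common part of delivery cost. A difference in therapist rate or group size would not cancel. The size in euros per QALY cannot be derived from the documents, and both numerical examples only show the mechanism. This concerns a secondary aim and what may be concluded from it.

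**What to change.** Amend the Aim 2 text under Analyses by aims.

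1. **Study 2.** Replace the Mind-against-each-control ICERs with a full incremental analysis of TAU, support and Mind: rank by cost, remove dominated and extendedly dominated options, and compute ICERs between neighbours. Draw one acceptability curve for all three options from the same bootstrap samples of net benefit. Base any public-payer conclusion on this analysis, which includes TAU.
2. **Study 1.** State that the economic result is relative to a support group of equal scheduled therapist input and is not evidence of cost-effectiveness against usual care.

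The cost is wording and a small amount of extra analysis, with no new data. The downsides are a narrower economic claim for study 1, and wider uncertainty wherever TAU enters, since it is the smallest arm. That uncertainty should be shown.
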